## Methods/design

### Design Outline

This study is a prospective, randomized, single blind, balanced parallel-group (1:1) superiority trial with stratification by baseline comfortable gait speed (< 0.5 m/s and ≥ 0.5 m/s). The design includes concealed allocation during recruitment and screening, blinded outcome assessment and intention to treat analysis. Refer to Figure 1 for study design diagram.

**Figure 1 F1:**
[figure not shown]
**Study design and timelines**.

### Ethics

All study activities have been approved by the Research Ethics Boards of St. Joseph's Healthcare Hamilton (#6-2753), the Hamilton Health Sciences/Faculty of Health Sciences McMaster University (#07-054), and Joseph Brant Memorial Hospital, Burlington, Ontario.

### Participants

The target population of this trial is community-dwelling, ambulatory older adults with mild to moderate stroke-related walking dysfunction within twelve months of most recent stroke onset. In contrast to most previous trials [17,24,25,33,34], time since onset was limited to less than one year as it represents the period when patients are most likely to access community-based rehabilitation interventions. Seventy participants will be recruited from clients about to be discharged from inpatient acute and rehabilitation units and outpatient programs at two teaching hospitals in Hamilton, Ontario, Canada (St. Joseph's Healthcare Hamilton and Hamilton Health Sciences) and one community hospital, Joseph Brant Memorial Hospital, in the neighbouring community of Burlington. We expect that treating physiotherapists and other clinicians will refer the majority of potential participants; however, some individuals may self-refer in response to community advertisements. Following screening, individuals will be invited to participate if they meet the following criteria: 1) living in the community at time of entry into study, 2) at least 40 years old, 3) within 12 months of onset of a physician diagnosed ischemic or hemorrhagic stroke in any brain location (with or without evidence from diagnostic imaging), 4) able to walk 10 m without assistance with self-selected gait speed < 1.0 m/s (or typically use a walking aid), 5) able to follow a 2-step verbal command, 6) independent with community ambulation prior to most recent stroke, and 7) receive physician approval to participate in the study. Individuals with history of more than one stroke who meet all other inclusion criteria will be included in the study. Individuals will be excluded if they present with: 1) marked cognitive impairment (i.e. Mini Mental Status Exam < 24/30 or score less than predicted according to age and education level) [36], 2) severe visual impairment, 3) lower extremity amputation, 4) presence of serious unstable cardiac, medical or musculoskeletal conditions that would limit safe participation in walking exercise (as determined by physician screening and baseline assessment interview).

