**Methods/Design:**

A parallel, randomized controlled trial with stratification by baseline gait speed will be conducted. Allocation will be controlled by a central randomization service and participants will be allocated to the two active intervention groups (1:1) using a permuted block randomization process. Seventy participants will be assigned to one of two 15-session training programs. In MLWP, one physiotherapist will supervise practice of various overground walking tasks. Instructions, feedback, and guidance will be provided in a manner that facilitates self-evaluation and problem solving. In BWSTT, training will emphasize repetition of the normal gait cycle while supported over a treadmill, assisted by up to three physiotherapists. Outcomes will be assessed by a blinded assessor at baseline, post-intervention and at 2-month follow-up. The primary outcome will be post-intervention comfortable gait speed. Secondary outcomes include fast gait speed, walking endurance, balance self-efficacy, participation in community mobility, health-related quality of life, and goal attainment. Groups will be compared using analysis of covariance with baseline gait speed strata as the single covariate. Intention-to-treat analysis will be used.

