### Randomization

Participants will be randomly allocated to the two active intervention groups using a fixed allocation ratio of 1:1. Consistent with previous studies in this area [19,33], we anticipate the response to both training programs to be associated with pre-treatment walking ability and participants will be stratified by baseline comfortable gait speed (slow < 0.5 m/s and fast ≥ 0.5 m/) to minimize group imbalances on this variable [37]. In order to maintain recruitment balance between groups throughout the trial, a permuted block randomization process will be used within each strata using block sizes of at least 2 with all blocks divisible by 2 [38]. The randomization creation process (including block sizes) and resulting schedule will be set, held and managed by a central randomization service (Biostatistics Unit at St. Joseph's Healthcare Hamilton). Group assignment will be communicated by email to the research coordinator on a single participant basis after screening, written informed consent, and baseline assessments have been completed.

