### Sample size

Seventy participants will be recruited. The sample size has been calculated to reliably detect a 0.14 m/s between-group difference in gait speed change (assuming a standard deviation of 0.19 m/s) with 80% power at a 2-tail significance level of 0.05. Using self-selected gait speed as the primary outcome, this sample size has been estimated based on a range of change scores and standard deviation values reported in the literature. Reported differences in change scores between experimental and control interventions range from 0.9 m/s to 0.14 m/s and standard deviation in change scores range from 0.14 to 0.19 m/s [19,33,34,69,70]. Using a conservative estimate of standard deviation of change score of 0.19 and a difference between group change scores of 0.14 m/s, the minimal number of participants required for each treatment group is 29 participants. Dropout rates in previous studies have ranged from 7 to 20% [19,33]. Allowing for a 17% loss to follow up rate, the study will need to recruit approximately 35 participants into each group for a total of 70.

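### The primary ANCOVA leaves out time since stroke, which the protocol collects and itself calls a key baseline characteristic; adding it would gain precision at almost no cost (minor)

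*Protocol article*

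**What the plan says.** **Who enters.** The Participants section requires entry "within 12 months of onset of a physician diagnosed ischemic or hemorrhagic stroke in any brain location" and states no minimum time since onset. Participants are to be "recruited from clients about to be discharged from inpatient acute and rehabilitation units and outpatient programs", and must be "living in the community at time of entry into study" and able to walk 10 m without assistance. The section presents the window as deliberate: "In contrast to most previous trials [17,24,25,33,34], time since onset was limited to less than one year".

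**How they are allocated.** Under Randomization there is a "fixed allocation ratio of 1:1", and "participants will be stratified by baseline comfortable gait speed", cut at 0.5 m/s. No other stratification factor is used.

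**How the primary outcome is analysed.** The abstract gives an "analysis of covariance with baseline gait speed strata as the single covariate". The Primary Analysis section agrees: its two factors are intervention group and speed stratum (slow or fast).

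**Where time since stroke appears.** The general Statistical Analysis section plans adjusted regressions to examine the residual effect of key baseline characteristics and lists four: age, time since stroke onset, comfortable gait speed and training site. Table 3, which summarises the primary, secondary and sensitivity analyses, does not list these regressions. Table 2 collects stroke details at screening/baseline, and the 12-month criterion cannot be applied without the onset date.

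**The concern.** The window runs from shortly after hospital discharge to the end of the first year. Change in walking speed over a five- to seven-week programme may well differ between its two ends, whichever programme is given. A two-level speed stratum cannot separate a participant walking at 0.4 m/s soon after stroke from one walking at 0.4 m/s in month 11; both fall in the slow stratum.

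If time since stroke predicts post-intervention speed beyond the stratum, leaving it out of the primary model has two effects. The variation that it explains stays in the error term, so the standard error is larger than necessary. In any single randomization, a chance difference between the arms in recovery stage also carries through to the primary estimate. Both effects matter more in a trial planned at 80% power with 29 evaluable participants per arm than they would in a large one.

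**Working it through.** **Inputs from the protocol (Sample size section).** Difference 0.14 m/s, SD 0.19 m/s, two-sided 0.05, power 80%, 29 per arm, 17% loss, 35 per arm recruited.

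**Input assumed.** The correlation ρ between time since stroke and the outcome, after the terms already in the model, is not given. The values 0.1, 0.3 and 0.5 are shown.

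**1. Reproduce the planned size.** n per arm = 2(1.960 + 0.842)² × 0.19² / 0.14² = 28.9, so 29. Power at 29 per arm by the same normal formula is 80.1%. (The t-based formula gives 29.9, or 30.) With loss, 29 / 0.83 = 34.9, so 35 per arm and 70 in total. The stated figures hold.

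**2. Precision now.** SE = 0.19 × √(2/29) = 0.050 m/s; 95% half-width about 0.098 m/s. At 35 per arm the SE is 0.045 m/s.

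**3. Gain from adjustment.** Adjusted SD = 0.19 × √(1 − ρ²), at 29 per arm:

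| Assumed ρ | Adjusted SD (m/s) | Power | n per arm for 80% |
|---|---|---|---|
| none (as planned) | 0.190 | 80.1% | 29 |
| 0.1 | 0.189 | 80.5% | 29 |
| 0.3 | 0.181 | 83.7% | 27 |
| 0.5 | 0.165 | 90.0% | 22 |

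**4. How far chance imbalance can move the estimate that is not adjusted for time since stroke.** The between-arm difference in mean time since stroke has an SD of √(2/29) = 0.263 covariate SDs; its 95% limit is 1.96 × 0.263 = 0.515. Shift = ρ × 0.19 × 0.515:

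- ρ = 0.1: 0.010 m/s, 7% of the 0.14 m/s target
- ρ = 0.3: 0.029 m/s, 21%
- ρ = 0.5: 0.049 m/s, 35%

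These are shifts at the 95% limit, not typical ones. Each equals 1.96ρ standard errors, so even at ρ = 0.5 the shift is 0.98 of one SE.

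**5. Validity.** In 20,000 simulated null trials per setting (29 per arm, ρ = 0, 0.3 and 0.5, no stratum term), the rejection rate was 0.046 to 0.052 without adjustment for the covariate and 0.046 to 0.051 with it. The omission does not inflate the type I error.

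**6. Sensitivity to the SD.** The 0.19 m/s is an SD of change scores, whereas the primary model analyses post-intervention speed with a two-level stratum. Its residual SD is not given and may be larger. Suppose it were 0.25 m/s (assumption) and the effect of time since stroke in m/s were unchanged. Then ρ becomes ρ × 0.19/0.25, that is 0.076, 0.228 or 0.380. Power at 29 per arm goes from 56.8% to 57.1%, 59.1% or 63.5%, a gain of 0.2, 2.3 or 6.7 percentage points. At 0.19 m/s the corresponding gains are 0.4, 3.6 and 9.9 points.

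**The case against.** The strongest defence is that the plan is coherent. The abstract, Randomization and Primary Analysis sections agree: stratify on speed, then adjust for the stratum. The protocol justifies both that factor and the 12-month window. Every trial leaves some prognostic factor out of its primary model. Time since stroke is not ignored either, because an adjusted regression naming it is already planned, so readers would see whether it changes the result. All of this stands, and it is why the point is minor. It does not remove the case for using, in the primary model, a covariate that the protocol already holds and already calls key.

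Three stronger readings are tempting but unsupported.

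- **That the primary result would be biased.** It would not. Chance imbalance is part of the sampling error that the standard error measures. As a cruder illustration, assume half of the 70 are early after stroke and gain 0.10 to 0.20 m/s more than the rest. A gap of at least 20 percentage points between arms (7 of 35) then has probability 0.151. At exactly 20 points it moves the estimate by 0.20 × 0.10 = 0.02 to 0.20 × 0.20 = 0.04 m/s, still below the SE of 0.045 m/s at 35 per arm. The document gives neither the split nor the gain.
- **That the planning SD comes from the wrong population.** The Sample size section reports that "standard deviation in change scores range from 0.14 to 0.19 m/s [19,33,34,69,70"]. The Background describes references 33 and 34 as chronic-stroke trials, but reference 19 enrolled people within one year of stroke. The document does not show which source gave 0.19 m/s, and the plan took the top of the range. No error in the SD can be inferred.
- **That entry is effectively open from the day of stroke.** No minimum in days is stated, but community living, unassisted walking over 10 m, the cognitive threshold and physician approval all restrict very early entry.

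**Conclusion.** This is a minor point: an improvement available at almost no cost, not an error or a contradiction. The primary ANCOVA as written is valid but passes over a baseline variable that the protocol collects and names as key. Under the planning SD of 0.19 m/s and 29 per arm, the gain in power ranges from negligible (80.5% at ρ = 0.1) to material (90.0% at ρ = 0.5). It also removes a component of chance movement in the estimate of up to 0.010 to 0.049 m/s at the 95% limit of imbalance. All of these figures rest on an assumed correlation. They shrink if the speed stratum already carries part of the recovery-stage effect or if, for the same effect in m/s, the residual SD is above 0.19 m/s. If the association is weak, little is gained and almost nothing is lost.

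**What to change.** In the Primary Analysis section, add time since the most recent stroke at randomization to the ANCOVA as a prespecified continuous covariate (for example, log days), beside the speed term. Make the same change in the primary row of Table 3 if covariates are listed there, and reword the abstract so that the speed stratum is no longer described as the only covariate. The general Statistical Analysis section can keep its adjusted regressions for the remaining characteristics.

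The cost is a few words and one degree of freedom. No new data are needed, and eligibility, the single stratification factor and the total of 70 do not change. If the team prefers to leave the primary model alone, a weaker alternative is to name the already planned regression including time since stroke as the key supportive analysis of the primary outcome.

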### Randomization

Participants will be randomly allocated to the two active intervention groups using a fixed allocation ratio of 1:1. Consistent with previous studies in this area [19,33], we anticipate the response to both training programs to be associated with pre-treatment walking ability and participants will be stratified by baseline comfortable gait speed (slow < 0.5 m/s and fast ≥ 0.5 m/) to minimize group imbalances on this variable [37]. In order to maintain recruitment balance between groups throughout the trial, a permuted block randomization process will be used within each strata using block sizes of at least 2 with all blocks divisible by 2 [38]. The randomization creation process (including block sizes) and resulting schedule will be set, held and managed by a central randomization service (Biostatistics Unit at St. Joseph's Healthcare Hamilton). Group assignment will be communicated by email to the research coordinator on a single participant basis after screening, written informed consent, and baseline assessments have been completed.

### Experimental Intervention: Motor Learning Walking Program (MLWP)

The Motor Learning Walking Program is a program of varied overground walking-task practice based on theory and research from the fields of motor control, motor learning, neuroplasticity, and stroke rehabilitation. The following statements will be used to guide the implementation of the MLWP:

***1. Motor skill is the product of multiple systems, internal and external to the individual ***[39]. Skilled human walking arises from the distributed contribution of both internal (e.g., musculoskeletal, cardiovascular and central nervous system) and external systems (e.g. the environment). The characteristics of walking will vary depending on the specific task and environmental context in which it is performed. A comprehensive rehabilitation program must address the known demands of community walking [40].

***2. Learning is defined as a relatively permanent change in skill level (retention) and the ability to perform skill under varied conditions (transfer) ***[35]. ***Motor learning is typically specific to the conditions of practice***. Practice conditions should resemble the conditions of expected typical performance, including task characteristics, sensory motor conditions and information processing demands [35]. Repetitive task oriented practice of walking results in improved walking outcomes after stroke [20]. Training-induced neuroplasticity is specific to the trained movement or skill [41,42].

***3. Practice should be sufficiently intense***. Increased amounts of practice (repetitions) are typically associated with increased learning [35,42]. Increased practice of lower extremity focused activities is associated with improved recovery of walking after stroke [43].

***4. Practice must be sufficiently challenging and engaging***. Motor learning is enhanced when the learner is cognitively challenged during practice or training [44,45]. Cognitive effort may be facilitated through non-repetitive (random or serial) practice schedule, opportunity for self-evaluation and error correction through reduced augmented feedback presentation and minimal physical guidance, and increased task complexity [44-46]. Motor learning rather than simple motor activity or movement repetition is required to induce cortical and sub-cortical reorganization [42,46]. Practice must be interesting, meaningful, with the learner/client actively engaged in order to induce desired neuroplastic changes [42].

***5. Variable practice optimizes learning***. Practice of a skill under a variety of environmental and task conditions usually leads to improved retention and transfer of skill to novel performance conditions [35].

***6. The effect of variable practice is usually enhanced when practiced in a non-repetitive order ***[35].

### Content of the MLWP

At the first session, the therapist will spend 15 minutes to establish walking-related goals with the client. These goals will help inform the content and emphasis of the walking training program. Training will be organized to promote engagement in intense, repetitive practice of a variety of challenging, walking tasks. Practice will be cognitively effortful, encouraging participants to solve and re-solve the problems of walking in a variety of environmental and task conditions. Refer to Figure 2 for a graphic representation of the MLWP.

**Figure 2 F2:**
[figure not shown]
**Motor Learning Walking Program**. Every session includes all seven core tasks described in the centre circle. During or between sessions, the training physiotherapist may adjust the level of challenge of each core task by adding or removing one or more of the task complexity factors described in the outside circles.

#### Core Tasks

Participants will practice all walking tasks overground. At every session, the therapist will incorporate the following seven core tasks that reflect the typical demands of home and community ambulation [40,47]: 1) walk short distances, 2) walk prolonged distances or times (> 50 m or > 5 minutes), 3) steps, curbs and slopes, 4) obstacle avoidance, 5) transitional movements (e.g. sit to stand and walk), 6) changes in centre of gravity (e.g. pick up object from floor while walking) and, 7) changing direction/turning while walking.

#### Increasing Complexity of Walking Task Practice

Using the concepts described by Gentile in her Taxonomy of Task Analysis [48] the training therapist will make each of the core tasks more complex through the addition of concurrent mental, verbal or physical tasks, adding a time restraint, altered terrain and/or lighting, increased duration, reduced predictability and/or performance of walking in a mobile environment.

The therapist will adjust the difficulty of practice tasks based on their assessment of the participant's ability to perform the task safely without maximum physical assistance.

Tasks will be practiced in a serial or random order, moving from task to task, avoiding repetition of one station more than two times in a row. Feedback will be delayed and participants will be asked to self-evaluate their performance on a task and develop strategies to improve performance. When feedback is given, it will include either knowledge of results (e.g. time taken to complete a specific task) or knowledge of performance (e.g. step length, stance time) types of feedback [49]. The therapist will only provide hands-on guidance or assistance when required for safety, or for initial completion of the basic task. Specific handling or facilitation techniques will not be used to affect quality of gait. Participants will practice walking tasks with and without their preferred gait aid. Tasks will be practiced in the physiotherapy gym and/or more natural settings inside and outside the hospital (e.g. courtyard, sidewalks, hospital lobby). The tasks will be designed to encourage inclusion of both lower limbs during practice (e.g. reciprocal stepping up stairs). Each session will last 45 minutes including intermittent rest periods as required. Participants will practice three times a week for five weeks for fifteen sessions. Refer to Figure 2 for a graphic representation of the Motor Learning Walking Program.

### Comparison Intervention: Body Weight Supported Treadmill Training (BWSTT)

Participants in the control group will practice walking on a treadmill according to a protocol based on an intervention described by Sullivan et al. [33] and Duncan et al. [50]. Based in the CPG theory of stepping control and recovery [51], the focus of this intervention is to provide participants with an opportunity to practice many repetitions of the normal gait cycle. Within a 45-minute session, participants will practice walking for up to 30 minutes at a time on the treadmill. Participants will train using the LiteGait system (harness and mechanical overhead suspension) and the GaitKeeper treadmill (Mobility Research Inc.). All participants will initiate training with 30% of their total body weight supported. A maximum of 40% body weight support will be provided during training. As recommended in the literature [33,52], participants will practice walking on the treadmill at speeds above their preferred overground walking speeds, preferably at or above 0.89 m/s (or 2.0 mph). Physical guidance will be provided by 1 to 3 therapists at the participant's pelvis, and/or their limbs to increase gait symmetry, facilitate weight shift, increase hip extension during stance, and to correct foot placement. Verbal feedback related to the participants gait pattern (knowledge of performance) will be provided frequently and concurrent to participants walking on the treadmill. Continuous visual feedback will also be provided via a full-length mirror. Participants will be discouraged from placing their hands on the LiteGait or treadmill handles during training. Body weight support, feedback, and guidance will be weaned, and treadmill speed adjusted according to a clinical decision making algorithm modified from a training algorithm described for individuals with spinal cord injury by Behrman et al. [53]. A comparison of key elements of the MLWP and BWSTT are provided in Table 1.

**Table 1 T1:** Description of experimental and comparison interventions

Learning Variable/Principle	Motor Learning Walking Program	Body Weight Supported Treadmill Training
**Amount of Practice/Intensity**	Up to 40 minutes of walking activity per session 15 sessions over 5 weeks	Up to 30 minutes treadmill walking per session 15 sessions over 5 weeks
**Specificity Of Practice**	Reflects task and environmental demands of community walking	High repetitions of near normal gait cycle on treadmill
**Variable Practice**	Variable practice of different overground walking tasks	Single task practice - walking on treadmill
**Practice Order**	Random or serial order, moving through different tasks returning to each task at least once.	Blocked or mass practice of single task of walking on treadmill
**Augmented** **Feedback**	Encourage self-evaluation through delayed, intermittent and summary feedback KP and results KR provided	Continuous, immediate visual (mirror) and/or verbal feedback. Focus on KP, specifically related to posture and gait pattern
**Instructions**	Instructions provided related to the goals of the task. Emphasis on problem solving, discovery of alternate ways to complete walking tasks.	Instructions regarding performance of near normal gait pattern
**Physical Guidance**	Physical guidance provided for safety, or initial completion of basic task early in learning. Emphasis on allowing participants to make and attempt to correct errors.	Frequent guidance of one to three trainers at pelvis, hemi and non-hemi-limb to guide position and timing Up to 40% body weight support provided through harness - weaned according to performance Handle use discouraged Errors prevented or minimized
**Training Personnel**	Physiotherapist × 1	Physiotherapist × 1 plus 1 to 2 other physiotherapists or physiotherapy assistants
**Training Setting**	In hospital physiotherapy department, other parts of hospital and outdoors	In hospital outpatient department on treadmill
**Training Speed**	Practice of comfortable and fast walking	Will train at, or above target speed 2.0 mph (0.89 m/s) as soon as participant is able
**Use Of Walking Aid/Orthoses**	Practice with and without orthoses and walking aid	Practice without walking aid, may use orthoses if necessary

KP = knowledge of performance, KR = knowledge of results

For experimental and control interventions, blood pressure (BP), heart rate (HR) and rating of perceived exertion (RPE) will be measured at the beginning, during rest periods and at the end of every treatment session. During training, exercise intensity will be reduced if HR exceeds 70% of age predicted maximal heart rate (220 - age) or RPE is greater than 13 on the Borg RPE scale. If resting BP exceeds 180 mmHg systolic and/or 100 mmHg diastolic, the exercise session will be stopped and their physician notified. This information will be recorded allowing comparison between groups. Patients will also wear the StepWatch 3^© ^step activity monitor during training sessions, and mean number of steps taken during the sessions recorded as a measure of amount of task-related practice.

In the event of missed sessions, participants will be allowed a maximum of seven consecutive weeks to complete as many of the fifteen sessions as possible. Considering that previous studies have demonstrated changes in walking skill following 12 [24,25,33,34] and 18 sessions [19] over 4 [24,25,33,35] to 6 [19,34] weeks, we expect that a training frequency of 2 to 3 sessions per week for a total of 15 sessions will be result in improved walking skill in our participants.

To minimize the risk of contamination, separate training physiotherapists will deliver the Motor Learning Walking Program and the BWSTT program. All therapists will undergo a standardized training program prior to treating study participants on their own. The principal investigator will monitor ongoing competence and adherence through session observation, case discussions and documentation reviews. In order to minimize the impact of expectation bias, training therapists and participants will be blinded to the hypotheses of the investigators regarding which of the two interventions is expected to result in superior outcomes. To avoid co-intervention, participants will be asked to refrain from attending physiotherapy for their balance or walking limitations during the study intervention period. Participants will be questioned at post-intervention and follow up measures regarding their participation in physiotherapy outside of the study.

